# Feasibility of a specific task-oriented training versus its combination with manual therapy on balance and mobility in people post stroke at the chronic stage: study protocol for a pilot randomised controlled trial

**DOI:** 10.1186/s40814-021-00886-0

**Published:** 2021-07-27

**Keywords:** Stroke, Neurological physiotherapy, Manual therapy, Task-oriented training, Postural balance, Walking, Mobility limitation, Range of motion, Ankle joint

## Abstract

**Background:**

Large studies have shown that stroke is among the most relevant causes of acquired adult disability. Walking and balance impairment in stroke survivors often contribute to a restriction in daily activities and social participation. Task-oriented training (TOT) is an effective treatment strategy and manual therapy (MT) is used successfully to enhance ankle joint flexibility in this population. No study, however, has compared TOT against its combination with MT in a randomised controlled trial. Aims of this pilot study are therefore to explore the feasibility of a full-scale RCT using predefined feasibility criteria. Secondary aims are to explore the preliminary effects of specific TOT with a combined specific TOT-MT versus a control group in people post stroke.

**Methods:**

This is a protocol of a 4-week prospective randomised controlled parallel pilot trial in people post stroke at the chronic stage with limited upper ankle joint mobility and an impairment in balance and mobility. At a German outpatient therapy centre using 1:1:1 allocation, 36 patients will be randomised into one of three groups: 15-min talocrural joint MT plus 30-min specific TOT (group A), 45-min specific TOT (group B), and controls (group C). Training will be goal-oriented including tasks that are based on daily activities and increased in difficulty utilising predefined progression criteria based on patients’ skill levels. Interventions will be provided face-to-face 2 times per week, for 4 weeks, in addition to 20-min concurrent x4 weekly home-based training sessions. Data will be collected by blinded assessors at baseline, post-intervention and 4-week follow-up. The primary outcome will be feasibility assessed by recruitment, retention and adherence rates, compliance, adverse events, falls and the acceptability of the intervention. Secondary outcomes will be walking speed, single and dual tasking functional mobility, ankle range of motion, disability and health-related quality of life.

**Discussion:**

Feasibility provided, results from this study will be used to calculate the sample size of a larger randomised controlled trial to investigate the effects of specific TOT and specific TOT-MT compared to a post stroke control group.

**Trial registration:**

German Clinical Trials Register, DRKS00023068. Registered on 21.09.2020, https://www.drks.de/drks_web/navigate.do?navigationId=trial.HTML&TRIAL_ID=DRKS00023068.

**Supplementary Information:**

The online version contains supplementary material available at 10.1186/s40814-021-00886-0.

## Introduction

Walking and balance impairment contribute to functional disability experienced by many stroke survivors, frequently affecting social participation [1]. Postural control deficits in the stroke population are related to reduced walking speed and dynamic mobility, greater gait variability and fall rates [2]. Functional walking limitation and motor control deficits in people post stroke are associated with the upper motor neuron syndrome [3]. Foot drop is often observed in stroke patients, induced by spasticity, weakness of the foot dorsiflexors, shortening of plantarflexors and ankle range of motion (ROM) limitation [4, 5]. Such a complex movement disorder requires differentiated therapy strategies, to address both the structural and functional movement limitations. Upper ankle joint, i.e. talocrural manual therapy (MT) [6] and MT with movement, leads to increased joint ROM alongside balance improvements [7, 8].

Few studies have investigated the effects of talocrural mobilisation and conventional functional training in chronic stroke patients, showing conflicting results. Kluding and Santos compared the effects of functional practice with ankle joint mobilisations against functional practice alone [9]. Study results showed increased ROM of the ankle joint after MT. Improved weight transfer to the paretic side during sit-to-stand was seen after functional training whereas combined practice impaired weight transfer. An and Jo explored active talocrural mobilisation as an add-on to conventional physiotherapy in chronic stroke patients. In contrast to the aforementioned study, improvements in ankle ROM, strength, mobility and weight transfer to the paretic side were observed post-intervention [10].

From a neurological physiotherapy and motor learning perspective, it appears relevant practising meaningful tasks to enhance motor control and dynamic mobility. Specific strategies are needed to promote motor learning and long-term improvement in motor function [11]. Task-oriented training (TOT) is established in stroke rehabilitation, including a variety of trained activities and progression strategies [12–14] where patients actively interact with the environment striving for a defined and meaningful goal [15]. While the training is individually targeted, progression should be predefined. Patients will be invited to choose training tasks according to their preference and activities of daily living (ADL). In addition, effective training programmes involve a specific, outstanding, challenging, repetitive, variable and intensive task practice [16–18]. It appears logical that patients who consider the training programme useful and designed for their daily needs engage more intensively. Finally, significant motor learning literature has suggested adopting an external focus of attention during the training, directed to the desired outcome, a device or the environment [19]. Conventional physiotherapy may not meet this criterion without explicit intention.

To our knowledge, only one study has investigated the effects of a specific TOT as compared to a combined wrist joint MT and upper-limb TOT approach [20]. Hand function and joint mobility significantly improved after the combined training than compared to TOT alone. This cross-sectional study did not assess long-term outcomes. A randomised controlled trial (RCT) with a follow-up period is therefore needed which applies the combined intervention protocol to the lower limbs. This pilot study will be conducted to evaluate the feasibility of the methods of a larger trial and to explore the preliminary effects of a specific TOT, versus its combination with talocrural mobilisation on balance, mobility, ankle ROM, number of falls and health-related quality of life (HRQoL) in people post stroke.

The research question is as follows: Is a full-scale RCT feasible to investigate the effects of specific TOT versus its combination with talocrural MT on balance, mobility, ankle ROM, number of falls and HRQoL, based on the feasibility criteria of recruitment, retention and adherence rates, compliance, adverse events, falls and acceptability of the intervention? The null hypothesis is that a larger main study need not be performed.

### Objectives

Explore the feasibility of a larger RCT that will validate the study results and investigate the effects of specific task-oriented mobility and balance training versus its combination with MT on dynamic balance in people at the chronic post stroke stage. Secondary objectives will be to investigate the preliminary effects of the same training on dynamic balance, mobility, walking speed, upper ankle ROM, number of falls, disability and HRQoL.

### Study design and location

The supporting CONSORT checklist for this study is available as additional information; see Additional file 1. This will be a prospective randomised controlled pilot trial in chronic stroke patients comprising two parallel intervention groups and a control group. The primary outcome will be feasibility assessed by recruitment, retention and adherence rates, compliance, adverse events, falls and the acceptability of the intervention. Block randomisation will use permuted blocks of 3 and 6 and 1:1:1 allocation. A CONSORT flow diagram is shown in Fig. 1. The study location will be a physiotherapy practice in rural Germany, chosen because the home-based intervention has been designed for stroke patients at the chronic stage who have regained at least a minimum level of mobility.

**Fig. 1 Fig1:**
[figure not shown]
Flow diagram

## Methods

### Patients

#### Inclusion criteria

Patients eligible for the trial must comply with all of the following at randomisation:
≥18 years of agePeople who have had an ischaemic or haemorraghic stroke at least 6 months prior to study startLimited dorsiflexion ROM in the upper ankle joint on the hemiparetic side: maximum 0° active ROM; maximum 5° of passive ROMCapability to independently transfer from a seating to a standing position without an assistive device—use of the hands is allowedAbility to independently walk without an assistive device for at least 10 mConfirmation by the principle investigator (PI) of the study (medical clinician) that there are no contraindications connected to exposure to active training

#### Exclusion criteria

Patients will be excluded from the study if they meet any of the following criteria:
Any contraindication to MT (ankle instability, ankle inflammation or traumas, etc.)Any not fully recovered injuries of the musculoskeletal systemWalking impairment due to orthopaedic reasons, e.g., due to previous surgery in the lower extremity regionRelevant ROM reduction of the hip or knee jointsAny cognitive or communication impairment hindering participation in this pilot study according to the study PI (dementia, severe aphasia, being under legal guardianship, etc.). Screening for cognitive decline will be performed using the Mini Mental State Examination (MMSE) [21], with a score of ≤24 representing cognitive impairment [22]. Cognitive dysfunction will also be evaluated clinically by treating neurologists who refer patients to the study. Dementia will be defined as a patient’s report or the clinical presence of typical symptoms such as impaired thinking, memory, orientation, attention, calculating, reasoning, self-management, language skills, problem solving, visual perception and ability to perform everyday activities.Diabetes mellitusRheumatic diseasesChronic pain treated by drug therapyHistory of previous stroke with persistent, impairing neurological symptoms (defined by a Modified Rankin Scale score (mRS) [23] of ≥3)Comorbidity hindering participation, according to the study PI (life expectancy <12 months, cancer, severe heart insufficiency, etc.)mRS score ≥4Pregnancy

#### Recruitment and informed consent

The study will be advertised using recruitment flyers at medical and physiotherapy practices within a 30-km radius of the study location. Written informed consent will be taken by a medical doctor as per German legislation and oral and written information will be provided for the patients by a neurological physiotherapist. Additionally, a trained physiotherapist who holds a Master’s degree in musculoskeletal physiotherapy and is studying for another Master’s degree in neurological physiotherapy (KT) will explain the study intervention in detail. Oral and written information will be given in comprehensible lay language and questions answered regarding study procedures.

#### Randomisation, concealment of allocation and blinding

Randomisation will be stratified on age, the most relevant predictive factor for balance and mobility change in people post stroke (strata: under 70; 70 and over) [24]. Stratification will help ensure similarity between the intervention and control groups regarding age. Mixed randomisation will be performed on the two age groups, consisting of simple and blocked randomisation [25] and applying the following procedure: (1) permuted blocks of three or six are generated with an online random number generator (Sealed Envelope, London, UK); (2) after having randomised a predefined, small and varying number of patients to the three groups, a block size of an interspersed uneven block of 5–11 is chosen, with predefined differences in the sample sizes of the allocated groups; (3) a simple randomisation sequence is generated using the same random number generator; and (4) uneven distribution of As, Bs and Cs provided, another set of permuted blocks of three or six is generated. Details of blocking will be kept in a separate, unavailable document.

Allocation concealment will be performed to avoid allocation bias. Each patient will receive a unique identification number (ID). Based on the randomisation list, sequentially numbered sealed opaque envelopes including group allocation numbers A, B and C will be created for each stratum, given to patients in the order they are recruited. Patients will be asked not to discuss their allocation until study completion. Should a patient nonetheless report details of his or her group allocation, the patient will be informed about the importance of blinding and asked again not to tell anybody about the allocation. In such a case, a second assessor will perform the assessments. The allocation sequence and sealed envelopes will be created by a researcher who is not involved in the study procedures (BS). Patients will be assessed for eligibility and enrolled by the chief investigator (FS) and assigned to the intervention or control groups by the care provider, a physiotherapist-researcher (KT). Outcome assessors (EB; EK) will be blinded to the group allocation of patients. It will not be feasible to blind the care provider.

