### Interventions

Eligible patients will be randomised into one of three groups:
Patients in group A (Gp A) will receive a 15-min talocrural joint MT directed at the dorsiflexion before a 30-min specific task-oriented mobility and balance training 2 times per week. Further, a 20-min home-based ankle mobilisation and TOT programme 4 times per week, for 4 weeks.Patients in group B (Gp B) will receive a 45-min specific task-oriented mobility and balance training 2 times per week. Further, a 20-min home-based TOT programme 4 times per week, for 4 weeks.Patients in group C (Gp C) will receive no specific treatment.

All patients will receive their usual care involving appointments with the treating neurologist or other medical doctors and any medication such as anticoagulants or antihypertensive drugs. Interventions in groups A and B will be provided face-to-face by an experienced physiotherapist (KT). Patients will be asked to perform the home-based training on the intervention-free days only and given free choice of one rest day per week.

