### Data management and data protection

Data quality will be promoted by duplicate (10MWT) or triple measurements (ankle ROM measures, utilising two different measurement approaches). Only the PI and care provider will be aware of the demographic data and have access to the pseudonymisation documents. Double data entry will be performed. Data will be verified by conducting spot checks of value ranges and field types for certain data fields, and logical checks will also be performed (e.g. the order of visits). When checking value ranges, the fields will be checked for permitted values. Field type checks concern whether the values entered fit the field definition (e.g. numerical fields). Any discrepancies found will be rectified.

For the qualitative analysis of interviews, coding will be performed by two independent coders (KT, BS). Codes will be discussed and if a consensus cannot be reached, a third researcher will provide support (FS). Post interview, the interviewer will review and ascertain that all answers have been understood correctly. Patients will be asked to provide feedback on the findings. For the report, patient quotations will be used, together with patient ID and group allocation.

German legislation states any study records and documents must be stored for a period of 10 years after the conclusion of the clinical study. Personal data will be collected, forwarded, stored and evaluated as part of this clinical study in accordance with the legal provisions of the General Data Protection Regulation (EU) 2016/679 (GDPR) and German Data Protection Act 2018 (BDSG).

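### One unblinded physiotherapist informs candidates, assigns groups and treats, so can guess the next arm somewhat better than chance; separate the roles and reconcile the two descriptions of the randomisation

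*Protocol article*

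**What the plan says.** Three sections of the protocol article give one person, marked by the same initials, three tasks.

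- **Recruitment and informed consent.** A neurological physiotherapist gives oral and written information and a medical doctor takes written consent. In addition, the physiotherapist who will deliver the treatment "will explain the study intervention in detail".
- **Randomisation, concealment of allocation and blinding.** The chief investigator assesses eligibility and enrols. Patients are then "assigned to the intervention or control groups by the care provider, a physiotherapist-researcher". Of this person the article says: "It will not be feasible to blind the care provider".
- **Interventions.** "Interventions in groups A and B will be provided face-to-face by an experienced physiotherapist". This is again the same person.

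The allocation method is described twice. Study design and location says: "Block randomisation will use permuted blocks of 3 and 6 and 1:1:1 allocation". The randomisation section describes a mixed scheme within two age strata: permuted blocks of three or six, then an interspersed uneven block of 5–11 with planned imbalance, a simple randomisation sequence, and further permuted blocks. That section adds: "Details of blocking will be kept in a separate, unavailable document". Envelopes are sequentially numbered, sealed and opaque, with one series per stratum, and are used in order of entry. They and the list are "created by a researcher who is not involved in the study procedures".

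**The concern.** Sealed envelopes hide the next slip but not the history. Whoever assigns and treats can keep a tally by stratum. According to Data management and data protection, the care provider also has the demographic data and the pseudonymisation documents, so a candidate's age stratum is known too. Any blocked sequence makes the next arm partly predictable from such a tally. If the same person speaks to candidates before they are randomised, the warmth of the explanation, or the timing of entry, could vary with the arm thought to be next.

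Two results are at stake. The first is the preliminary between-arm effects, which are meant to size the main trial. The second, less directly, is the recruitment rate, which is one of the feasibility criteria. How predictable the sequence is depends on which description of the scheme is followed, and the article gives two.

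**Working it through.** **Inputs from the article.** Three arms at 1:1:1; two age strata; 36 patients, 12 per arm. The article's own inflation for 20% attrition reproduces: 36/(1 − 0.20) = 45. No stated figure is in dispute here; 36 and 45 serve only to set the stratum size.

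**Assumptions.** The split between strata is not given, so 18 per stratum (36/2) and 22 per stratum (45/2, rounded down) were used. Block sizes 3 and 6 were taken as equally likely. For the mixed scheme, permuted runs of 3, 6 or 9 patients alternate with unbalanced simple-randomised blocks of 5–11. The real layout is withheld, so this is indicative only.

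**Simulation.** There were 20,000 sequences per scheme. The guesser sees all past allocations in the stratum and either applies Bayes' rule on the belief that blocks are of 3 or 6, or names the least-filled arm.

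| Scheme | Bayes guess, n = 18 / 22 | Least-filled arm, n = 18 / 22 |
|---|---|---|
| Simple randomisation | 33.4% / 33.4% | 33.4% / 33.4% |
| Mixed scheme (assumed layout) | 44.2% / 44.0% | 42.9% / 42.0% |
| Permuted blocks of 3 and 6 only | 57.0% / 56.4% | 57.1% / 56.2% |

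Under blocks of 3 and 6 alone, about 8% of assignments are known with certainty. Under the mixed scheme, the Bayes guesser feels at least 95% sure for about 5% of assignments and is right in only 54–57% of those, because the uneven blocks break the pattern.

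**From guess to bias.** Let g be the hit rate. Let delta be the prognostic difference between candidates who enter when a given arm is expected and those who enter otherwise. That arm is expected for a share g of the patients who receive it and for (1 − g)/2 of those who receive another given arm. The difference between the two arms is therefore shifted by

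[g − (1 − g)/2] × delta = (3g − 1)/2 × delta.

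- Mixed, least-filled arm: (3 × 0.429 − 1)/2 = 0.14; at 0.420 it is 0.13.
- Mixed, Bayes guess: (3 × 0.442 − 1)/2 = 0.16.
- Blocks of 3 and 6 only: (3 × 0.571 − 1)/2 = 0.36.

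**Scale.** The article gives no value for delta. If delta is assumed to be 0.2 to 0.5 SD, the factor 0.14 gives a shift of 0.03 to 0.07 SD. With 12 per arm, the standard error of a difference in means is √(1/12 + 1/12) = 0.41 SD. Under the mixed scheme the shift is thus well below sampling error, even with every guess acted on.

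**The case against.** The strongest reply is that the therapist does not control entry. The chief investigator enrols, a medical doctor takes consent, another physiotherapist gives the oral and written information, and the envelopes are numbered, sealed and opaque. This stands, and it leaves only the explanation and the timing of entry as routes. The article describes neither being used in this way. The effects are also labelled preliminary and the primary outcome is feasibility, so the consequence is limited. The effect on the recruitment rate cannot be quantified from the document.

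A reader might infer more than the text supports:

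- **That the next assignment is readily predictable, at 57%.** That figure belongs to the one-line summary in Study design and location. The fuller procedure in the randomisation section was built to break block prediction.
- **That the therapist speaks before consent and hands out the envelopes.** The first is implied by the section heading and the second by the word for assigning. Neither is stated.
- **That publishing block sizes on 27 July 2021, during recruitment (1 April to 31 October 2021), defeats the secrecy rule.** The secrecy sentence closes the very paragraph that prints three, six and 5–11. The withheld details can be read as block order, switch points and planned imbalances, which are not published.
- **That the list maker's later role adds selection bias.** Data management and data protection says "coding will be performed by two independent coders", and one of them is the list maker. Coding interviews about patients' experience gives no hold over enrolment or allocation. The statement of non-involvement is only loosely worded.

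**Conclusion.** The point holds as a weakness in the separation of roles, together with an inconsistency between two sections. One unblinded person informs candidates, assigns and treats, and so knows past allocations by stratum. The next arm can be guessed about 42–44% of the time against 33% by chance, on an assumed layout of the mixed scheme. The possible range runs from 33% (all simple) to about 57% (all permuted 3/6). The resulting bias in the preliminary between-arm effects is about 0.14 delta, or 0.16 with the better guesser. Both are upper-end values because they assume that every guess is acted on, and delta is unknown. The figure rises to about 0.36 delta only if the design section describes the real scheme. This is a modest risk that is cheap to remove, not evidence that allocation was compromised.

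**What to change.** Make these changes with existing staff and the existing list, for patients still to be randomised:

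1. The neurological physiotherapist already named under Recruitment and informed consent gives all information before randomisation. The treating therapist explains the training only after allocation. This is the main step, because the tally then cannot reach candidates.
2. The researcher who made the list, or another team member who does not treat, holds the envelopes. The next one is released only after eligibility, consent and the t1 baseline are logged.
3. Align Study design and location with the mixed scheme in the randomisation section, and drop the block sizes from the former.
4. Reword the statement that the list maker has no part in study procedures, since that researcher codes interviews. This is a wording correction only; coding need not be delayed.

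Do not regenerate the remaining list. The mixed scheme already varies the blocks, and a new sequence could disturb its rebalancing step in a trial of 36. The cost is protocol wording, a change in who does what, and a short wait for each release. No extra staff or patients are needed.
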